### Trial interventions

Both the active eTNS and sham stimulation will be given by the Monarch eTNS System (NeuroSigma, Inc., Los Angeles CA). Sham stimulation will serve as a control group. Stimulation will be provided by an external pulse generator, placed close to the patient’s bed and attached with thin wires to a disposable patch electrode placed on the forehead. Bilateral stimulation of the first branch of the trigeminal nerve will last for approximately eight hours nightly over the course of four weeks. Patches will be removed every morning. Power will be provided by 9 V lithium batteries, which will be replaced with a newly charged battery every day.

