### Discontinuation or modification of interventions

Compliance is defined as completing the treatment in 70% of the nights during the four weeks. Abruption of treatment is only accepted if it happens less than four nights in a row. One whole night is considered of a minimum duration of five hours of uninterrupted stimulation (see feasibility outcomes below).

Families are advised to withhold from using the device in case of fever. The families are free to withdraw their informed contest at any time without providing an explanation. The trial investigators are authorised to terminate participation in case the participant is diagnosed with one of the predefined exclusion criteria or if the patients encounter intolerable adverse reactions.

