#### Outcomes

### Feasibility outcomes

Feasibility outcomes will be measured at the end of the 4-week treatment period.The proportion of participants assessed for eligibility who consent to inclusion and randomizationWe will compare the number of eligible participants to the number of randomized participants. We will accept a difference above 50% (95% CI 40.2% to 59.6%). A larger difference can impose difficulties with recruitment in a future randomized trial.Compliance with the interventionWe will calculate the number of participants fulfilling treatment for both the group receiving sham and active eTNS. Compliance with treatment will be defined as completing the treatment in 70% (95% CI 58.4% to 81.6%) of the nights during the four weeks. Abruption of treatment can only be accepted if it happens within less than four nights in a row.Acceptability of the interventionThe acceptability of the intervention will be assessed using a semi-structured qualitative interview guide with predefined questions:How did you feel about administering and controlling the device?How did your child feel about receiving this type of treatment?How was it for your child to receive home-treatment with the device in addition to other strategies provided by the clinic?Did the intervention have any influence on the relationship between your child and the parents/siblings/school/friends?Completion of follow upCompletion of follow-up will be defined as completing the assessment of the primary exploratory clinical outcome at the end of the intervention. The number of participants with completed outcomes will be compared to the number of participants in total. If the number of participants completing this assessment is above 90% (95% CI 82.4% to 97.6%), this will be acceptable for a future full-size trial. If the number of participants completing the assessment is below 75%, this will introduce serious problems with the interpretation of the results.Use of concomitant treatmentAny concomitant treatment or changes in medication will be assessed for each participant and subsequently evaluated for the two groups at the end of the trial.

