### Sample size and power consideration

We will include 60 participants which corresponds to approximately 20% of the sample size needed for the full-scale randomized superiority trial. This corresponds to a power of 48% for the primary outcome (ADHD core symptoms) in this feasibility trial, indicating that the risk of type 1 error is high, and any finding thus may only be considered as exploratory.

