### Randomisation and blinding

The randomization procedure will be computer-based and provided by The Copenhagen Trial Unit (CTU). The allocation sequence generation will be performed using block sizes of varying lengths concealed for the investigators. Randomization will be stratified by use of ADHD medication compared to no use of ADHD medication at entry. The allocation ratio will be 1:1. Both participants, personal and outcome assessors will be blinded to treatment allocation. Only one investigator will have access to group assignments. This investigator will also be the main person involved with any technical difficulties the families may experience during the trial. Premature disclosure of blinding may occur in case of adverse events where unblinding in considered essential for the safety and further treatment of the patient.

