The Monarch eTNS system has the advantage of being a small device, with a simple interface that is easy to manage by a layperson. Treatment is controlled at home by the parents and actively applied during nighttime [16]. Given these advantages, eTNS may be appealing to patients and parents. In accordance, we expect that a high number of participants will complete the trial and that families will find this intervention acceptable. We are aware that in any trial it is difficult to meet a criterion of 100% of participants completing the trial, and thus we consider a completion rate of 90% or above as sufficient for proceeding with a larger trial. This level of completion has been chosen to accommodate a real-life setting, in which we accept that circumstances not related to the trial may arise, that necessitate termination of participation. In terms of compliance, we will consider an abruption of treatment less than four nights during the four-weeks of treatment as acceptable. This feasibility trial will also be used to determine whether the planned recruitment strategy is adequate. In our preliminary study by Lykke Huus et al. [46], we chose to solely include treatment naïve patients yet found that recruitment was hindered by the families needing immediate support. In the present feasibility trial, we expect that also including patients on stable medication may improve recruitment. By including these patients, the external validity of our trial will improve. Our preliminary study also showed that parents considered the device to be user-friendly and that they felt confident in using the device based on the information they were provided [46]. The general experience with the device, including its practical use will once again be evaluated in this trial, but now within a larger study group.

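### The compliance definition carries a confidence interval that belongs to a share of 60 participants, and no acceptable share of compliant participants is stated

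*Protocol article*

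**What the plan says.** Compliance is described in three places in the protocol article.

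- Feasibility outcomes: "Compliance with treatment will be defined as completing the treatment in 70% (95% CI 58.4% to 81.6%) of the nights during the four weeks". The same item says that the number of participants fulfilling treatment will be counted in the sham group and in the active group. It adds that an interruption is acceptable only if it is shorter than four consecutive nights.
- Discontinuation or modification of interventions: "Compliance is defined as completing the treatment in 70% of the nights during the four weeks". There is no interval here. The limit on consecutive nights is repeated, and a completed night is defined: "One whole night is considered of a minimum duration of five hours of uninterrupted stimulation".
- Discussion: "In terms of compliance, we will consider an abruption of treatment less than four nights during the four-weeks of treatment as acceptable".

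For comparison, the completion item under Feasibility outcomes reads: "If the number of participants completing this assessment is above 90% (95% CI 82.4% to 97.6%), this will be acceptable for a future full-size trial". It adds that completion below 75% would seriously hamper interpretation.

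**The concern.** Two quantities are involved. One is the share of nights that one participant must complete to count as compliant. It is a rule fixed in advance, with no sampling error. The other is the share of participants who meet that rule. It is estimated from the trial and does have a confidence interval. The article prints an interval on the first quantity and gives no criterion for the second.

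Feasibility is the trial's stated objective, and the Background makes a full-sized trial conditional on it. The Abstract lists compliance among the feasibility outcomes and notes that home use requires a high degree of it. As written, compliant participants will be counted but there is no stated number to judge the count against. Whether compliance was good enough could then be decided after the data are seen.

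**Working it through.** **Inputs**

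- 70% and its interval, 58.4% to 81.6%: Feasibility outcomes.
- Total sample size 60: "We will include 60 participants which corresponds to approximately 20% of the sample size needed for the full-scale randomized superiority trial" (Sample size and power consideration).
- About 30 per arm: "The allocation ratio will be 1:1" (Randomisation and blinding).
- Treatment period: stimulation "will last for approximately eight hours nightly over the course of four weeks" (Trial interventions), taken here as 28 nights.

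**Step 1. Reproduce the printed interval.** The Wald interval is p ± 1.96 × √(p(1 − p)/n). With p = 0.70 and n = 60:

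1.96 × √(0.70 × 0.30 / 60) = 1.96 × 0.0592 = 0.116, so 58.4% to 81.6%.

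Both limits match to one decimal. In a search over every n from 5 to 2,999, only n = 60 gave both.

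**Step 2. Try the alternatives at 70%.**

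| Denominator and method | 95% interval |
|---|---|
| 28 nights of one participant, Wald | 53.0% to 87.0% |
| 60 × 28 = 1,680 participant-nights, Wald | 67.8% to 72.2% |
| 30 participants (one arm), Wald | 53.6% to 86.4% |
| 60 participants, Wilson | 57.5% to 80.1% |
| 42/60 participants, Clopper-Pearson | 56.8% to 81.2% |

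None reproduces the printed limits, and in particular neither night-based denominator does.

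**Step 3. Cross-check with completion.** With p = 0.90 and n = 60: 1.96 × √(0.90 × 0.10 / 60) = 0.076, so 82.4% to 97.6%, as printed. The same formula and denominator were used, but there the percentage is a share of participants, so the interval fits.

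**Step 4. Read the compliance text literally.** The cut-off is 0.70 × 28 = 19.6, so at least 20 nights. The printed limits would be 0.584 × 28 = 16.4 and 0.816 × 28 = 22.8 nights. A range of 16.4 to 22.8 nights means nothing as part of a definition.

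**Step 5. Look for a group-level criterion.** Feasibility outcomes gives only a count per group. Discontinuation or modification of interventions and the Discussion give only rules for the individual participant. None states a required share of compliant participants.

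**Step 6. Compare the interruption statements.** The two methods sections limit consecutive nights. The Discussion sets the limit over the whole four weeks. If the Discussion means total missed nights, it allows at most 3, so at least 25/28 = 89% of nights must be completed. The 70% rule allows 28 − 20 = 8 missed nights. The two cannot both define compliance.

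**The case against.** The strongest reply is that this is a drafting slip with little effect. The individual rule is clear without the interval, because Discontinuation or modification of interventions gives it cleanly and defines a completed night. Participants can be classified and counted as written, and no sample size, randomisation, efficacy or safety procedure depends on the interval. This stands, and it limits the severity.

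A second reply is that a missing threshold is an omission which the full protocol or the analysis plan may fill. Acceptability and concomitant treatment have no numerical threshold either, and the wording around the 50% recruitment figure is itself unclear, so completion is the only clean comparator. This stands in part. But the article does not simply leave the matter open: it prints an interval that belongs to another quantity, and a later document would have to correct that text, not just expand it.

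Two stronger readings are tempting, and the article supports neither. A reader might infer that the printed interval overstates the precision of the arm results, since the half-width at 70% is 11.6 points for 60 participants and 16.4 points for 30. The article promises only a count in each group and never says that the 60-participant interval will be applied to an arm. A reader might also conclude that the group target is 70% of participants. The interval suggests it, but the text never says so.

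**Conclusion.** The point holds as an error of attachment. The arithmetic of 58.4% to 81.6% is right for 70% of 60 participants, but the interval is printed on a within-participant cut-off that cannot have one. The article states no acceptable share of compliant participants, although completion of follow-up has one. The interruption statements also conflict: 8 missed nights under the 70% rule against at most 3 on the total-nights reading of the Discussion.

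This should be fixed, but it does not threaten the conduct of the trial. The conclusion assumes 28 nights of treatment and, for the per-arm figure, exactly 30 participants per arm. That a 70% group target was intended is an inference from the interval, which the sponsor must confirm.

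**What to change.** 1. State the participant-level definition of compliance once, without a confidence interval.
2. State separately the share of participants who must be compliant for a larger trial to be judged feasible, with its denominator. If the sponsor intended 70% of all 60 participants (42/60), the printed 58.4% to 81.6% belongs here. If the criterion applies per arm, the Wald interval at 70% with 30 participants (21/30) is 53.6% to 86.4%. If another share is meant, give that share and its own interval.
3. Reconcile the interruption statements in Feasibility outcomes and in Discontinuation or modification of interventions with the one in the Discussion. Which rule applies is for the sponsor to decide.

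The cost is a change of wording in the protocol, carried into the statistical analysis plan. No change to sample size or data collection follows from it. The group-level share should be fixed before compliance data are examined.

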### Safety and adverse events

Parents will be able to report directly to a dedicated investigators not involved in data analysis, with any concerns regarding potential adverse events or other safety issues during the trial. Adverse events will be measured by an adverse events rating scale at the end of treatment [29]. Height, weight and vital signs will be assessed at baseline and again following the four weeks of treatment.

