### Inclusion criteria

7 to 17 years of age at the time of trial enrolment.A clinical diagnosis of ADHD according to criteria for ICD-10: F90.0, F90.1, F90.8, F98.8C [25].The ADHD diagnosis must be verified by the Diagnostic and Statistical Manual for Mental Disorders (DSM-5) [26] using The Schedule for Affective Disorders and Schizophrenia for School-aged Children (K-SADS) [27].A total score above 24 on the ADHD rating scale (ADHD-RS) at baseline.Signed informed consent from parents/legal caretakers and from the patients aged ≥ 15.

We will include treatment-naïve patients, patients who previously have received stimulant medication, and patients in stable, ongoing stimulant medication (methylphenidate or dexamphetamines/lisdexamphetamine) during the time of the trial.

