### Participant timeline

Eligible participants will be identified by clinicians working at the respective trial sites. They will ask the families whether they are willing to be contacted by the trial researchers for further information. The trial researcher will send a letter of information and request permission to follow-up with a phone call. Following the phone call, an in-person meeting will be scheduled, in which both oral and further written information will be provided. If the families wish to participate, a second in-person meeting is scheduled. At this second meeting, informed consent is obtained as well as a standard diagnostic—and health evaluation alongside baseline assessment and HRV measurements. The child is finally included in the trial, granted they meet the inclusion criteria following the health – and diagnostic evaluation. Randomisation then commence, in which the participant is allocated to either active or sham eTNS.

They will then proceed to test the device for four weeks. Families will keep a logbook for daily reporting on how the previous night had gone by. Once a week, they will fill in an online questionnaire received by email related to the primary exploratory outcome and the reporting of any adverse events. This email will also contain questions regarding the use of the device and concomitant medication. In addition, the families will receive a weekly phone call from the trial researcher, to remind them to fill in the questionnaire and to allow the families to ask questions if needed. Families may also contact a trial researcher directly via phone throughout the trial period.

Following the four weeks, an in-person meeting is scheduled, in which the families and trial investigators meet to discuss and share their experience. During this meeting, exploratory outcomes will once again be assessed, alongside HRV measurements and the rating of any adverse events. The full participant timeline is seen in Fig. 1.

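### The text gives the adverse-event rating scale no baseline administration, so complaints present at entry cannot be told from new ones on that scale

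*Protocol article*

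**What the plan says.** Under Safety and adverse events, the Protocol article states: "Adverse events will be measured by an adverse events rating scale at the end of treatment". The same paragraph treats the physical measures differently: "Height, weight and vital signs will be assessed at baseline and again following the four weeks of treatment". Under Exploratory outcomes, the clinical outcomes are likewise assessed at baseline and at the end of the four weeks.

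Participant timeline matches this. The visit before randomisation comprises a diagnostic and "health evaluation alongside baseline assessment and HRV measurements", with no adverse-event scale named. At the meeting after treatment, "exploratory outcomes will once again be assessed, alongside HRV measurements and the rating of any adverse events".

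There are other routes for adverse events. Once a week, families complete a questionnaire "related to the primary exploratory outcome and the reporting of any adverse events". In addition, "Parents will be able to report directly to a dedicated investigators not involved in data analysis". The nightly logbook (Records of intervention) also asks about problems during the night.

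Inclusion criteria admit "patients in stable, ongoing stimulant medication" alongside treatment-naïve and previously treated children.

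**The concern.** A symptom scale given once, after treatment, records what is present then. It does not show what is new. Background reports headache, fatigue, and appetite and sleep disturbance from an earlier pilot study of this device. Children may bring such non-specific complaints to the trial, and those on stimulants may have them because of their medication. The earlier study enrolled only treatment-naïve children; this trial does not.

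The Discussion says the trial is meant to add to what is known about tolerability. The rate of each complaint per arm is the natural summary for that, and it is the summary that a missing baseline damages most. This is a matter of which data are collected, so an analysis plan cannot repair it later: a rating not taken before the first night cannot be recovered.

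**Working it through.** There is no figure in the article to reproduce. The check has two parts: the schedule, and an illustration of size.

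**Schedule, as the text gives it**

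| Measure | Before treatment | During | End of treatment |
|---|---|---|---|
| Height, weight, vital signs | yes | – | yes |
| Exploratory clinical outcomes | yes | some weekly | yes |
| Sleep questionnaire (CSHQ) | yes | weekly | yes |
| Heart rate variability | yes | – | yes |
| Adverse-event rating scale | none named | – | yes |
| Weekly questions, logbook, direct reports | – | yes | – |

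The last row can date a complaint within the four weeks but supplies no value from before treatment.

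**Illustration of size**

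From the article: 60 participants allocated 1:1, so 30 per arm. Assumed, with no source in the article:
- entry prevalence *b*, equal in both arms
- true onset among children free of the complaint of 20% (active) and 5% (sham)
- every entry complaint persists to week 4, and every complaint present is counted.

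Observed rate = *b* + (1 − *b*) × onset. The observed difference is then (1 − *b*) × (20% − 5%).

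- *b* = 10%: active 0.10 + 0.90 × 0.20 = 28.0%; sham 0.10 + 0.90 × 0.05 = 14.5%; difference 13.5 points.
- *b* = 30%: active 0.30 + 0.70 × 0.20 = 44.0%; sham 0.30 + 0.70 × 0.05 = 33.5%; difference 10.5 points.
- *b* = 50%: active 0.50 + 0.50 × 0.20 = 60.0%; sham 0.50 + 0.50 × 0.05 = 52.5%; difference 7.5 points.

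Complaints carried in from entry would number 60 × *b* = 6, 18 and 30. If onset is 5% in both arms, the observed difference is zero at every *b*.

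Power was computed for a two-sided 5% test with *n* per arm, where p̄ is the mean of the two rates:

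Φ{[d − 1.96 √(2p̄(1 − p̄)/n)] / √[(p_A(1 − p_A) + p_S(1 − p_S))/n]}

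With no complaints at entry (20% v 5%, n = 30) this gives 42%. That is not quite the right yardstick for the fix, because a baseline rating leaves only 30 × (1 − *b*) children per arm at risk of a new complaint. The fairer comparison is:

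| *b* | End-only, all complaints, n = 30 | New complaints among those free at entry (20% v 5%) |
|---|---|---|
| 10% | 24% | n = 27: 38% |
| 30% | 13% | n = 21: 31% |
| 50% | 8% | n = 15: 23% |

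The trial is not designed to test adverse-event rates. These powers only show the direction and rough size of the loss.

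**The case against.** The strongest reply is that the schedule is not fully visible. Participant timeline refers to Fig. 1 for the full timeline, and that figure was not available. The text says the scale is given at the end, without saying only then. The scale is identified only by citation, so it might itself ask about onset or change. This stands as a limit on the finding: a baseline rating could exist. The text as written still describes none, in two separate sections, while stating baselines for the other measures.

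Several safeguards are also real:
- Sleep has the CSHQ at baseline and weekly, and marked restless sleep is an exclusion.
- Weight at both visits is a partial check on appetite.
- The health evaluation before randomisation could pick up existing complaints.
- The logbook and weekly questions give dated reports.

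These narrow the gap mainly to complaints such as headache and fatigue, and partly appetite. They do not provide a pre-treatment rating on the same scale.

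Three stronger readings are tempting, and the article does not support them:
- A reader might infer that entry complaints will be counted as adverse events. No counting rule, adverse-event definition or item list is shown, and an analysis plan may set one. The complaints named here come from the background account of an earlier study, not from this trial's scale.
- A reader might infer that the comparison between arms is biased towards finding harm. Randomisation, sham control and stratification by ADHD medication give no reason to expect a false difference.
- A reader might claim a gain in effective sample size from baseline adjustment. That needs a continuous score, which the article does not describe.

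**Conclusion.** The point holds in limited form. As the text describes it, the scale cannot distinguish complaints present at entry from those arising on treatment. The consequences are possible inflation of the per-arm rates and dilution of a real difference by the factor 1 − *b*, with no false difference expected. For *b* between 10% and 30%, an observed 5% onset rate would read as 14.5% to 33.5%, and a 15-point difference as 13.5 to 10.5 points. These sizes rest on the assumed prevalence, full persistence of entry complaints and a count of every complaint present. If complaints resolve or a rule excludes known ones, the effect is smaller. Feasibility outcomes sets no adverse-event threshold for proceeding to the larger trial, so no stated decision rule is affected. This is a cheap improvement to safety data that can be made only prospectively.

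**What to change.** Give the same adverse-event rating scale at the existing baseline visit, before the first night of stimulation. Report by arm the items that are new or worse than at baseline. For new complaints, use the children free of that item at entry as the denominator, and show worsening separately. If the scale yields a score, use its baseline value as a covariate in the week-4 comparison.

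If Fig. 1 already lists a baseline rating, no new data are needed; amend Safety and adverse events and Participant timeline to say so. For any participants already treated without a baseline rating, report the absence as a limitation.

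The cost is one short form, a few minutes per family, at a visit that already takes place.
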